## Abstract

The ability to remember future intentions (i.e., prospective memory) is influenced by attentional control. At the neuronal level, frontal and parietal brain regions have been related to attentional control and prospective memory. It is debated, however, whether more or less activity in these regions is beneficial for older adults’ performance. We will test that by systematically enhancing or inhibiting activity in these regions with anodal or cathodal high-definition transcranial direct current stimulation in older adults. We will include n = 105 healthy older volunteers (60–75 years of age) in a randomized, double-blind, sham-controlled, and parallel-group design. The participants will receive either cathodal, anodal, or sham high-definition transcranial direct current stimulation of the left or right inferior frontal gyrus, or the right superior parietal gyrus (1mA for 20 min). During and after stimulation, the participants will complete tasks of attentional control and prospective memory. The results of this study will clarify how frontal and parietal brain regions contribute to attentional control and prospective memory in older healthy adults. In addition, we will elucidate the relationship between attentional control and prospective memory in that age group. The study has been registered with ClinicalTrials.gov on the 12th of May 2021 (trial identifier: NCT04882527).

## Introduction

The ability to perform an intended action at a future point in time is referred to as prospective memory. How well we remember these intentions seems to depend on attentional control, which enables us to direct (or shift) attention and to inhibit responding to distractions [1, 2]. Attentional control predicts laboratory prospective memory across all ages [3–6]. At a neuronal level, there may be a link between attentional control and prospective memory as well since, for example, the inferior frontal gyrus as well as the superior parietal lobe were active during both tasks in younger and middle-aged adults (see [7] for a meta-analysis). There is an ongoing debate, however, whether increased or decreased activity in these brain regions is beneficial for older adults’ attentional control [8–12] or prospective memory [13–16]. In the context of ageing, understanding the differential role these areas have for both cognitive functions would be important. To this end, modulating activity in these areas during these tasks can provide dynamic insights. This may help to develop further current models of how they are involved in attentional control and prospective memory in healthy ageing and to predict what goes wrong in diseases. So far, activity in the left or right inferior frontal gyrus or the superior parietal lobe was modulated during attentional control tasks. It was found that activity in the right hemisphere was particularly relevant for attentional control in both younger and older adults [17–21] although excitatory protocols (e.g., anodal stimulation) did not necessarily led to performance gains. For prospective memory, increasing activity in the left superior parietal lobe improved younger adults’ prospective memory more than increasing activity in the right superior parietal lobe [22, 23]. It is not completely understood, however, whether this effect generalizes to older adults, and/or whether modulating other brain regions such as the left or right inferior frontal gyrus has similar effects on prospective memory.

To answer these questions, we will systematically enhance or inhibit activity in frontal or parietal brain regions in healthy older adults during attentional control and prospective memory tasks. We will modulate activity in three areas; that is, the right superior parietal lobe, the right inferior frontal lobe or the left inferior frontal lobe. In order to replicate previous studies, we will test whether attentional control will predict laboratory prospective memory. In addition, we will test whether attentional control will also predict naturalistic prospective memory.

We hypothesize that the right inferior frontal gyrus and the right superior parietal lobe will be important for laboratory prospective memory as well as for attentional control. Modulation of the left inferior frontal cortex, however, will only lead to an improvement in prospective memory since attentional control seems particularly associated with the right hemisphere. Finally, we hypothesize that attentional control will predict laboratory prospective memory rather than self-reports or naturalistic prospective memory. Laboratory tasks share a similar setting and rely on timely motor responses while self-reports or naturalistic prospective memory tasks do not. To control for any effect of mood or agitation on cognition, we will examine current mood as well as the heart rate of all participants.

## Materials and methods

This study aims to test the contribution of frontal and parietal brain regions to attentional control and prospective memory in healthy older adults. We will conduct the study in a randomized, double-blind, sham-controlled, and parallel-group design (Fig 1). The study has been registered with ClinicalTrials.gov (Identifier: NCT04882527) and follows the SPIRIT guidelines [24].

**Fig 1 pone.0289532.g001:**
[figure not shown]
SPIRIT schedule of enrolment, interventions and assessments.

### Participants’ eligibility and recruitment

Participants will be recruited via flyers, newspaper advertisement, or newsletters. For an inclusion, they will need to be between 60–75 years of age, fluent in German, right-handers, non-smokers, with normal or corrected-to-normal vision, and no history of severe psychiatric or neurological disorders. In addition, their Montreal Cognitive Assessment score (MoCA) [25] will need to be ≥ 23 and their Geriatric Depression Score (GDS) [26] will need to be ≤ 6. To ensure comparable verbal intelligence, all participants will complete a German vocabulary test (Wortschatztest, WST) [27]. Exclusion criteria will be severe colour blindness, past head injuries, dermatosis, metal implants in the head-area, current or lifetime seizures, alcohol or drug abuse, intake of medication that interferes with cognition, as well as brain damage.

All participants will give written informed consent prior to testing. The Cantonal Ethics Committee Bern approved the study, which will be conducted according to the Declaration of Helsinki.

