### Randomization

A total of 105 healthy older adults will be included, stratified by age and sex. All participants will be randomly assigned to one of six experimental groups or the control condition (i.e., sham stimulation). They will receive anodal or cathodal high-definition tDCS of the right inferior frontal lobe, the left inferior frontal lobe, or the right superior parietal lobe, or sham. For sham stimulation, we will randomly place the electrodes over the same regions. Randomization will be done by JP based on a Matlab script written by TR (allocation ratio 1:5, stratified by age and sex). Neither JP nor TR will be involved in data collection. The study will follow a double-blind design, such that neither the participants nor the experimenter will be aware of the stimulation condition. Unblinding will occur at the end of data acquisition. Exceptions will only be allowed in case of adverse events.

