### Study procedure

All participants will be tested twice to differentiate learning effects from stimulation effects (Fig 2). All assessments will be done by the same examiners (NS, RM) at the University Hospital of Old Age Psychiatry and Psychotherapy at the University of Bern, Switzerland. On the first day of the experiment, we will test verbal intelligence [27], followed by an assessment of current mood (Profile of Mood States, POMS; Positive and Negative Affect Scale, PANAS) [28–30]. Then, the participants will put on a wearable device (Polar Verity Sense by Polar Electro Europe AG, polar.ch) on their left arm that will monitor their heart rate. Next, they will be asked about how many hours they had slept the night before and how awake and motivated they currently feel. Then, the attention network task and the prospective memory task will follow. Next, they will do a Go/No-Go task, a flexibility task, and a divided attention task (TAP) [31]. Finally, they will again rate their current mood and different naturalistic prospective memory tasks will follow. The second day of the experiment will be identical with the exceptions that we will apply stimulation for 20 min during the attention network task and the prospective memory task and that there will be no verbal intelligence test. At the end of the experiment, side effects, and the participants’ perception of the stimulation condition will be captured [32].

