We will include age as a covariate in all models since it significantly influenced prospective memory in our previous study [52]. We will control for any potential influence of mood or agitation on cognition and test, in an exploratory analysis, whether mood or heart rate of participants will influence attentional control or prospective memory. Further we examine, whether one of these two measures are modulated by non-invasive brain stimulation. For an assessment of heart rate, we will include changes in beats per minute (relative to baseline) between the start of stimulation until two minutes after its end (i.e., 22 minutes). Generalized estimated equations will then be used to test any longitudinal stimulation effects on heart rate during the stimulation session [53–55].

We will use R (version 4.2.1) with RStudio (version 2022.02.3) for statistical analyses with *p* < 0.05 considered statistically significant. We will correct for multiple-comparisons using Bonferroni-Holm correction. Whenever the assumptions of normality and homogeneity are not met, data will be transformed and/or non-parametric alternatives will be used. We will only analyse data of participants that attended both sessions.

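### The vocabulary score meant to make verbal intelligence comparable is used nowhere in the stated plan, which leaves the secondary regression of prospective memory on attentional control open to confounding by verbal ability

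*Protocol article*

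**What the plan says.** All references are to the protocol article.

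- **Participants' eligibility and recruitment.** The WST comes straight after two numeric thresholds, MoCA of at least 23 and "Geriatric Depression Score (GDS) [26] will need to be ≤ 6". Its purpose is stated as "To ensure comparable verbal intelligence, all participants will complete a German vocabulary test (Wortschatztest, WST"). No WST threshold is given. The language criterion is fluency in German.
- **Study procedure.** The test is given once, before any stimulation: "On the first day of the experiment, we will test verbal intelligence [27"].
- **Randomization.** "All participants will be randomly assigned to one of six experimental groups or the control condition (i.e., sham stimulation"). The strata are age and sex: "A total of 105 healthy older adults will be included, stratified by age and sex".
- **Statistical analysis.** "We will include age as a covariate in all models since it significantly influenced prospective memory in our previous study". Further, "We will control for any potential influence of mood or agitation on cognition". Verbal intelligence is not mentioned. Stimulation effects are tested with session as the within-subject factor and condition as the between-subject factor. The multiple linear regression of prospective memory on attentional control is described in the paragraph on secondary outcomes.
- **Introduction and Discussion.** The regression carries a stated hypothesis: attentional control should predict laboratory prospective memory, but not self-reported or naturalistic memory. The Discussion singles out this predictive value as a contribution of the study.

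**The concern.** Giving a test does not make people or groups comparable. A score does that only if it is used to select, to stratify or to adjust, and the article states none of these for the WST. It does state a covariate rule, with a reason for age and a mention of mood and agitation. The one characteristic that the eligibility section says should be comparable is missing from that rule.

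The consequence lies in the regression. It compares people with one another on two measured traits, so randomisation gives it no protection against a common cause. Verbal ability is a plausible one. The laboratory prospective memory task runs inside a series of semantic-category decisions on German word pairs, each shown for 3 seconds. The phone messages and questionnaires have no such time pressure. If verbal ability raises both attention scores and the laboratory score, part of its effect would be credited to attentional control. That could happen more for the laboratory task than for the others, which is the contrast the trial expects to find.

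**Working it through.** **1. Sample size used below.** Seven groups of 15 give 7 × 15 = 105, as the sample size section states.

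**2. Does leaving out the WST harm the stimulation comparison?** Scale the WST to SD 1.

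- The standard error of the difference between two arm means is √(2/15) = 0.365 SD, so the 95% range is ±1.96 × 0.365 = ±0.72 SD. One given pair differs by more than 0.5 SD with probability 17%.
- Over seven arms (200,000 simulated allocations), the gap between the highest and lowest mean averages 0.70 SD and exceeds 0.5 SD in 82%.
- These are chance gaps with mean zero, and a test under random allocation already allows for them. The seven-group F test (6 and 98 degrees of freedom) without a WST term was simulated 20,000 times for each assumed WST–outcome correlation:

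| Assumed correlation | Type I error, post scores | Type I error, change scores |
|---|---|---|
| 0 | 4.7% | 5.2% |
| 0.3 | 5.0% | 5.1% |
| 0.5 | 4.7% | 4.9% |

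The simulation standard error is √(0.05 × 0.95/20,000) = 0.15 percentage points. All values are compatible with 5%.

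- In addition, any stable additive effect of verbal ability cancels in the session-by-condition contrast, because everyone has an unstimulated first session.
- Adjustment would bring only precision. With 15 versus 15, two-sided 5% and 80% power (assumed), the detectable difference in post-stimulation scores is (1.96 + 0.84) × 0.365 = 1.02 SD. Multiplying by √(1 − r²) gives 0.98 at r = 0.3 and 0.89 at r = 0.5.

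**3. Does leaving it out matter for the regression?** Suppose attentional control and prospective memory each correlate r with verbal ability and have no other link. Their correlation is then r × r = r². By Fisher's z, the test statistic has mean atanh(r²) × √(105 − 3) = atanh(r²) × 10.10. The two-sided 5% test rejects with probability Φ(mean − 1.96) + Φ(−mean − 1.96).

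| Assumed r | Spurious correlation r² | Mean of z | Rejection rate |
|---|---|---|---|
| 0.1 | 0.01 | 0.10 | 5% |
| 0.2 | 0.04 | 0.40 | 7% |
| 0.3 | 0.09 | 0.91 | 15% |
| 0.4 | 0.16 | 1.63 | 37% |
| 0.5 | 0.25 | 2.58 | 73% |

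The rates are for one predictor and one outcome, before the planned Bonferroni-Holm correction, which would lower them. They take r as the correlation left after age.

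**4. Effect of adjusting.** In the same scenario the numerator of the partial correlation given verbal ability is r² − r × r = 0, so the rejection rate returns to 5%. In practice adjustment removes only the part of verbal ability that the WST captures.

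**The case against.** A reader might infer that the seven arms will not be comparable in verbal intelligence. The documents do not support this. Allocation is random, so the arms are comparable in expectation. The chance gaps in step 2 would arise for any unstratified variable in arms of 15, and they do not inflate the error of the stimulation test. That objection stands in full.

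A reader might also infer that the predictive analysis is confounded and that it is the trial's main analysis. Neither is shown. The regression is placed with the secondary analyses. The documents give no correlation between the WST and any outcome, and the tasks themselves give reasons to consider low values. The ANT measure is a within-person difference on arrow trials. Go/No-Go and the dual task use symbols, patterns and tones. The prospective memory cue is a font colour, and the category decision has to be held back on those trials. At r of 0.2 or less the effect is negligible. This stands too, as a limit on size.

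Two further arguments carry less weight. First, an association adjusted for age alone already answers whether attentional control predicts prospective memory. That is true of bare prediction, but the Discussion wants to use a difference in predictive value between task types to help explain the age–prospective memory paradox, and a common cause could produce such a difference. Second, a condensed article may leave covariates to an analysis plan that is not shown. A fuller plan may indeed include the WST. However, the article does set out a covariate rule, and that rule does not carry through the purpose stated in its own eligibility section.

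**Conclusion.** The point holds in a limited form. The article assigns the WST a purpose that no stated step delivers. The randomised stimulation comparison is unaffected in validity, and its models need no change. The secondary regression is open to confounding by verbal ability, possibly in the direction of the hypothesised contrast between laboratory and naturalistic tasks.

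The size cannot be fixed from the documents. Over assumed correlations of 0.1 to 0.5, the false-positive rate for one test runs from 5% (no effect) to 73%. This assumes equal correlations of both measures with verbal ability, no other link between them, all 105 participants analysed and no multiplicity correction. Severity is minor: the analysis is secondary and the magnitude is unknown, but the remedy is almost free.

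**What to change.** 1. In *Statistical analysis*, name the session-1 WST score as a prespecified covariate beside age in the regressions of laboratory, naturalistic and self-reported prospective memory on attentional control. Settle this before unblinding.
2. In *Participants' eligibility and recruitment*, change the stated purpose of the WST to: *to describe and adjust for verbal intelligence*.

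The cost is one degree of freedom per regression. With an intercept, age and one attention score, the residual degrees of freedom go from 105 − 3 = 102 to 101. No new data are needed, since the score is already planned for every participant before stimulation.

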### Randomization

A total of 105 healthy older adults will be included, stratified by age and sex. All participants will be randomly assigned to one of six experimental groups or the control condition (i.e., sham stimulation). They will receive anodal or cathodal high-definition tDCS of the right inferior frontal lobe, the left inferior frontal lobe, or the right superior parietal lobe, or sham. For sham stimulation, we will randomly place the electrodes over the same regions. Randomization will be done by JP based on a Matlab script written by TR (allocation ratio 1:5, stratified by age and sex). Neither JP nor TR will be involved in data collection. The study will follow a double-blind design, such that neither the participants nor the experimenter will be aware of the stimulation condition. Unblinding will occur at the end of data acquisition. Exceptions will only be allowed in case of adverse events.

### Study procedure

All participants will be tested twice to differentiate learning effects from stimulation effects (Fig 2). All assessments will be done by the same examiners (NS, RM) at the University Hospital of Old Age Psychiatry and Psychotherapy at the University of Bern, Switzerland. On the first day of the experiment, we will test verbal intelligence [27], followed by an assessment of current mood (Profile of Mood States, POMS; Positive and Negative Affect Scale, PANAS) [28–30]. Then, the participants will put on a wearable device (Polar Verity Sense by Polar Electro Europe AG, polar.ch) on their left arm that will monitor their heart rate. Next, they will be asked about how many hours they had slept the night before and how awake and motivated they currently feel. Then, the attention network task and the prospective memory task will follow. Next, they will do a Go/No-Go task, a flexibility task, and a divided attention task (TAP) [31]. Finally, they will again rate their current mood and different naturalistic prospective memory tasks will follow. The second day of the experiment will be identical with the exceptions that we will apply stimulation for 20 min during the attention network task and the prospective memory task and that there will be no verbal intelligence test. At the end of the experiment, side effects, and the participants’ perception of the stimulation condition will be captured [32].

**Fig 2 pone.0289532.g002:**
[figure not shown]
Study procedure. There will be two assessments with similar setups. Only during the second assessment, participants will receive high definition-transcranial direct current stimulation (HD-tDCS) for 20 minutes with 1 milliamp.

### Attention network task (ANT)

With the attention network task, we will assess three aspects of attention: Alerting, orienting, and executive control [33]. We will use an adapted version of the original task (Fig 3) [34] and present stimuli with PsychoPy3 (version 2021.1.3). During the task, participants will see a row of five arrows on a screen and they will need to press one of two buttons to indicate the direction of the central arrow (i.e., left or right). The arrow can be surrounded by squares (neutral trials) or by flanker arrows that can point either to the same direction (congruent trials), or to the opposite direction (incongruent trials). The arrow can either appear above or below a fixation cross. A correct identification of the direction of any arrow requires attentional control since participants will need to inhibit responses to irrelevant flanking arrows and, at the same time, shift their attention either above or below any target location. In some trials, the arrow will be preceded by a cue. That cue can appear at the central fixation cross or both above and below it (i.e., double cue), which would indicate a neutral condition since no spatial cue will be provided. Sometimes, however, that cue will indicate where the next arrow will appear by either appearing below or above the central fixation (spatial cue condition). The task will consist of 144 trials with each combination of cue (no, double, middle, spatial) and stimuli (top neutral right/left, top congruent right/left, top incongruent right/left, bottom neutral right/left, bottom congruent right/left, bottom incongruent right/left) to be presented three times (4 cue types * 12 stimuli types * 3 repetitions = 144 trials). Instructions will be provided orally and in writing. All participants will train the task until they are able to provide a total of five correct responses. The training will be done immediately before the task starts.

**Fig 3 pone.0289532.g003:**
[figure not shown]
Attention network task. Participants will need to indicate the direction of a central arrow by button press. Flanking arrows (congruent or incongruent to the central arrow) or squares will need to be ignored. Arrows can be preceded by a cue or not. If a cue is present, it can appear at the centre (central cue) or both above and below the centre (double cue). It can also appear either above or below the fixation at which the arrow is going to appear (single cue).

We will assess alerting by calculating the difference between reaction times in trials with double cues and trials without any cues. For orienting, we will compare reaction times in trials with spatial cues to trials with central cues. For executive control (i.e., controlling), we will calculate the difference in response times between congruent flanker trials to incongruent flanker trials. The controlling variable will be of primary interest in our statistical analysis.

